##### Analysis of secondary endpoints:

Secondary safety endpoints: Between treatment arms differences in each safety endpoints measured as change in domain specific EPIC scores at a specific time points (*i.e.,* end of RT, 3, 6, 12, 24, and 60 months) from base line will be evaluated using t-test or Wilcoxon rank sum test whichever is more appropriate. The domain specific EPIC scores measured over time will also be modeled using a linear mixed effects model with fixed effects including time points, treatment arm, Gleason score, baseline PSA, T-stage, age, race, and a random intercept. Between treatment arms differences in GI and GU EPIC scores at 2 years adjusting for baseline scores and other covariates will be assessed using analysis of covariance (ANCOVA). Results from the primary unadjusted analysis and covariates adjusted analysis are expected to lead to similar conclusions. Otherwise, further investigation concerning possible heterogeneous subgroup effects and/or the impacts of missing values will be carried out to ensure that meaningful conclusions can be made.Secondary efficacy endpoints: For competing-risk endpoints such as PCSM, local failure (LF), regional failure (RF), TTP, and DM, Gray’s cumulative incidence method will be used with death as a competing risk for LF, RF and DM and death not due to prostate cancer for PCSM and TTP. OS and FFBF will be estimated by the Kaplan–Meier method and compared between arms with the log-rank test. Cox regression will be used to obtain hazard ratios (HRs) for OS and TTP. Fine and Gray’s regression will be used for the endpoints with competing risks. Adjusted HRs and the respective 95% confidence interval will be computed. Baseline PSA, stratification variables (baseline EPIC score and ADT status), age, race, and other covariates (Gleason, T-stage), will be adjusted for as appropriate in this analysis.

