#### Secondary endpoints

1. Compare patient-reported GI symptoms using the EPIC questionnaire at the end of RT and 3, 6, 12, and 60 months from end of treatment.2. Compare patient-reported GU symptoms using the EPIC questionnaire at the end of RT and 3, 6, 12, and 60 months from end of treatment.3. Compare time to progression (TTP) where progression is defined as the first occurrence of biochemical failure (BF), local failure, regional failure, distant metastasis (DM), institution of new unplanned anticancer treatment, or death from prostate cancer (PCSM).4. Compare freedom from biochemical failure (FFBF) and TTP rates with an alternate PSA ≥ PSA nadir + 2 ng/mL definition of BF.5. Compare local failure, regional failure, salvage therapy (*i.e.,* institution of new unplanned anticancer treatment), DM, PCSM, and overall survival (OS) rates.

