### Statistical analysis

#### Sample size and accrual

The primary objective of this study is to determine if 5 fractions of MRgRT does not increase GI or GU toxicity over 20 fractions of MRgRT. The primary endpoints are change scores in the bowel (GI) or urinary (GU) domains of the EPIC. The change scores will reflect the 2-year score minus the pre-treatment (baseline) score. It is hypothesized that the EPIC mean change score will be no worse in the 5-fraction arm than it is in the 20-fraction arm for both GI and GU toxicity. The sample size is calculated based on a non-inferiority design. The non-inferiority margins are set to be a change score of 6 points for the GI symptoms and 5 points for the GU symptoms. The standard deviation of the change scores are assumed to be 13.2 for the GI symptoms and 10.5 for the GU symptoms based on estimates in the RTOG 0415 trial [29]. This level of change in scores seems to be clinically meaningful. A sample size of 122 with 61 in each arm will provide 80% power for the GI endpoint and 83% power for the GU endpoint to detect non-inferiority using a one-sided, two-sample t-test with 0.05 level significance. Adjusting for a projected 10% EPIC/non-compliance rate, we will accrue and randomize a total of 136 patients (68 per arm). The primary endpoint analysis will occur approximately 4 years after study activation.

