#### Data analysis

##### Analysis of primary endpoints

The co-primary endpoints are GI and GU toxicity as measured by the bowel and urinary EPIC domains, respectively. The change scores, calculated as baseline score subtracted from 2-year score, will be analyzed using a non-inferiority t-test based on the prespecified non-inferiority margins with a significance level of 0.05. If the data are determined to be non-normal, a Wilcoxon test may be used instead. All patients with EPIC bowel and urinary domain scores will be included in the primary endpoint analysis. The EPIC scoring manual will be followed which requires ≥ 80% of items in a domain to be completed in order to obtain a score for that domain.

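### The supplementary mixed model for EPIC scores, as listed, has no arm-by-time term and no baseline score, so it gives one visit-averaged arm difference that matches no listed endpoint

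*Protocol article*

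**What the plan says.** All of this is in the protocol article.

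- **Secondary endpoints.** The GI item reads "Compare patient-reported GI symptoms using the EPIC questionnaire at the end of RT and 3, 6, 12, and 60 months from end of treatment". The GU item is worded the same way.
- **Analysis of secondary endpoints, visit comparisons.** The arms are compared on change from baseline at each of these visits: "end of RT, 3, 6, 12, 24, and 60 months". On the choice of test, the article says that these differences "will be evaluated using t-test or Wilcoxon rank sum test whichever is more appropriate".
- **Same section, longitudinal model.** The model is an addition to those tests: "The domain specific EPIC scores measured over time will also be modeled". Its form is given in full only here: "linear mixed effects model with fixed effects including time points, treatment arm, Gleason score, baseline PSA, T-stage, age, race, and a random intercept". The response is the score, not the change score.
- **Same section, 2-year adjusted comparison.** This is a separate ANCOVA: "Between treatment arms differences in GI and GU EPIC scores at 2 years adjusting for baseline scores and other covariates will be assessed using analysis".
- **Analysis of primary endpoints.** A non-inferiority t-test on the 2-year change, with this population: "All patients with EPIC bowel and urinary domain scores will be included in the primary endpoint analysis".
- **Evaluation of randomization and blinding.** Baseline EPIC bowel and urinary scores, pelvic radiotherapy and androgen therapy are the stratification factors, chosen because they are expected to be associated with the primary outcome.

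**The concern.** A model with main effects of time and arm only assumes that the two schedules differ by the same amount at the last day of radiotherapy and five years later. The article's own discussion separates acute from late side effects, and the secondary endpoints are visit-specific. The single coefficient corresponds to none of them.

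The handling of baseline adds to this. The response is the score and no baseline EPIC term is listed. If pre-treatment scores enter as responses, differences expected to be zero under randomisation are averaged into the arm effect. If they do not enter, the model ignores the most obvious predictor of later scores. Nodal radiotherapy and ADT are also absent, while Gleason score and T-stage are present. The efficacy models in the same section do name stratification variables (baseline EPIC score and ADT status).

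What is at stake is a supportive analysis. It is nevertheless the only listed EPIC analysis that would keep patients with partial follow-up, because the t-tests and the ANCOVA need a score at the visit concerned.

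**Working it through.** **Plan's own figures.** The article gives no figure for the mixed model. The sample-size figures reproduce and are not in dispute. With 61 per arm, one-sided 0.05 and the noncentral t on 120 df, power is 80.3% for GI (margin 6, SD 13.2; stated 80%) and 83.4% for GU (margin 5, SD 10.5; stated 83%). The total is 122 / 0.90 = 135.6, so 136.

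**Formula.** Let d_k be the true arm difference at visit k (5-fraction minus 20-fraction; negative is worse for 5 fractions). With complete, balanced data on K visits and a random intercept, the arm coefficient without interaction estimates the plain mean, (d_1 + ... + d_K) / K.

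**Patterns on the visits listed in the analysis section.** The differences are assumed, for illustration only.

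| Pattern | End RT | 3 mo | 6 mo | 12 mo | 24 mo | 60 mo | Six post-baseline visits | With one baseline zero |
|---|---|---|---|---|---|---|---|---|
| Early | -10 | -6 | -3 | -1 | 0 | 0 | -20/6 = -3.33 | -20/7 = -2.86 |
| Late | 0 | 0 | 0 | -1 | -6 | -8 | -15/6 = -2.50 | -15/7 = -2.14 |

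In the early pattern the model reports about -3 at 24 months, where the truth is 0. In the late pattern it reports -2.1 to -2.5, where the truth is -6. Trial Procedures collects EPIC at screening and again on the first day of radiotherapy. If both enter as responses, the late pattern gives -15/8 = -1.88.

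**Two opposite patterns, one answer.** Take the visits up to 24 months under six-monthly follow-up: end of RT, 3, 6, 12, 18 and 24 months.

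- Late: 0, 0, 0, -2, -4, -6. Mean -12/6 = -2.0; with a baseline zero, -12/7 = -1.71.
- Early: -6, -4, -2, 0, 0, 0. Mean -12/6 = -2.0; with a baseline zero, -12/7 = -1.71.

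The GI margin is 6 (Sample size and accrual: "change score of 6 points for the GI symptoms and 5 points for the GU symptoms"). The coefficient is the same for a 24-month difference of that size and for none.

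**Simulation check.** The early pattern was simulated with 61 per arm and 60 replicates. Between-patient and residual SDs were each assumed to be 9.3, so the change-score SD is 9.3 × √2 = 13.2.

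- *Post-baseline visits only.* Without interaction: -3.51. With arm-by-visit, in visit order: -9.93, -6.13, -3.51, -1.39, -0.30, 0.19. Their mean is -21.07/6 = -3.51, the same value.
- *Baseline as a response.* Without interaction: -2.75. With arm-by-visit, from baseline on: 0.12, -10.00, -6.12, -2.76, -0.63, 0.14, 0.02. Their mean is -19.23/7 = -2.75, again the same.

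The departures from theory (-3.51 against -3.33; -2.75 against -2.86) are simulation noise. For the first, the standard error of one coefficient is √[2 × 9.3² × (1 + 1/6) / 61] = 1.82, or 1.82/√60 = 0.23 over 60 replicates. The interaction model recovers the pattern; the listed model returns only its average.

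**The case against.** The strongest reply is that nothing decisive rests on this model.

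- **Visit-specific comparisons.** A reader might infer that the secondary endpoints cannot be estimated. The document does not support that. It assigns them to t-tests or Wilcoxon tests on change from baseline, and the adjusted 2-year comparison to ANCOVA. The mixed model is an addition with no visit contrast assigned to it. This stands.
- **Non-inferiority.** A reader might infer that diluting late toxicity tilts the trial towards the shorter schedule. It does not. The primary conclusion comes from the t-test on 2-year change, the interim rule uses 6-month change scores, and no margin attaches to the mixed model. Nor has the averaging a fixed direction: the early pattern counts against the 5-fraction arm at 24 months. This stands too.
- **Missing data.** A reader might infer that the model is the promised missing-data check. The article plans to look into missing values only if unadjusted and adjusted results diverge, and does not name this model for it. That use is a proposal here.
- **Open list.** The terms are introduced as included, not as exhaustive, and the SAP is not shown and may add the interaction. This limits the point to the model as listed. It does not remove it: the article gives seven fixed effects and the random-effect structure, and names stratification variables for the efficacy models but not here.

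**Conclusion.** The point holds for the supplementary mixed model as listed. It yields one arm difference averaged over acute and late visits, which answers none of the listed endpoints and may be too large or too small at any one visit. In the assumed patterns on the listed visits it is wrong at 24 months by about 3 points one way (-2.86 or -3.33 against 0) or 3.5 to 3.9 points the other (-2.50 or -2.14 against -6).

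These sizes rest on assumed trajectories and complete, balanced data. With dropout, the average would lean towards the visits that more patients attend, usually the early ones. The primary analysis, the visit-specific tests, the ANCOVA, the power and the sample size are untouched. This is a free improvement to a supportive analysis, not a threat to the trial's main conclusion.

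**What to change.** Restate the longitudinal model, for each EPIC domain, as follows:

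- visit as a categorical factor, with an arm-by-visit interaction;
- baseline domain score as a covariate, or baseline kept as a response with its mean constrained equal across arms, stating which;
- the stratification factors nodal radiotherapy and ADT, beside the covariates already listed;
- the arm difference and its confidence interval reported at each visit.

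Designate the 24-month contrast as a supportive missing-at-random check on the complete-case primary t-test. The covariance structure can be left to the SAP.

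The cost is a changed model statement and a few more parameters: over six post-baseline visits, six arm differences instead of one. Each is less precise than a pooled average, but each answers a question the protocol asks. No new data, no extra patients and no change to the primary test are needed.

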### Evaluation of randomization and blinding

This study will employ a randomized phase II non-inferiority design to compare 5 fractions of ultra-fractionated MRgRT versus 20 fractions of moderately hypofractionated MRgRT in the salvage setting for prostate cancer patients after prostatectomy. Patients will be stratified according to baseline EPIC bowel and urinary domain scores (*i.e.,* high bowel score and high urinary score vs. high bowel score and low urinary score vs low bowel score and high urinary score vs. low bowel score and low urinary score) as well as pelvic radiotherapy and androgen therapy (*i.e.,* yes vs. no), for these factors are expected to be associated with the primary outcome. Within each strata, patients will be randomized 1:1 to receive 5 fractions or 20 fractions using permuted block randomization. The trial schema is displayed in Fig. 1.

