##### General concomitant medication and supportive care guidelines

Androgen deprivation therapy (ADT) and pelvic nodal irradiation will be administered for patients with PSA > 0.4 ng/ml, high Decipher score (> 0.6), or pathologically positive lymph nodes [25–27]. ADT should consist of a luteinizing hormone-releasing hormone (LHRH) agonist or antagonist and be initiated prior to and within 6 months of starting radiotherapy and not exceed 24 months in duration.

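### Freedom from biochemical failure (FFBF) gets only a log-rank test with no strata named and no hazard ratio, although randomisation is stratified by ADT and pelvic nodal RT; a minor, free improvement for a secondary endpoint.

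*Protocol article*

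**What the plan says.** **Randomisation.** Under Evaluation of randomization and blinding, allocation is 1:1 in permuted blocks within strata. These are four baseline EPIC groups "as well as pelvic radiotherapy and androgen therapy". The reason given is "for these factors are expected to be associated with the primary outcome".

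**Who gets ADT and nodal RT.** The concomitant medication section ties both to PSA above 0.4 ng/ml, a high Decipher score or pathologically positive nodes. ADT must "not exceed 24 months in duration".

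**Analysis.** Under Analysis of secondary endpoints, methods are assigned endpoint by endpoint:

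- OS and FFBF: Kaplan-Meier curves, "compared between arms with the log-rank test".
- The Cox model is reserved for two endpoints, and FFBF is not one of them: "Cox regression will be used to obtain hazard ratios (HRs) for OS and TTP".
- The competing-risk endpoints are modelled by Fine-Gray; those listed as such are PCSM, local failure, regional failure, TTP and distant metastasis.
- Adjusted HRs use baseline PSA, "stratification variables (baseline EPIC score and ADT status"), age, race, Gleason score and T-stage. These "will be adjusted for as appropriate in this analysis".

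FFBF is a separately named secondary endpoint (Secondary endpoints, item 4) but appears in neither regression list. Nodal RT, a randomisation factor, is absent from the stratification variables named for adjustment.

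**The concern.** FFBF is the endpoint most directly exposed to ADT. Its event is defined by PSA, ADT suppresses PSA, and the indications for ADT and nodal RT are themselves markers of disease risk. If hazards differ between these groups, a log-rank test that pools them attenuates the arm contrast. Because allocation was balanced within the same groups, its type I error also falls below the nominal level.

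The trial asks whether the shorter schedule is no worse. On that question attenuation is not a safeguard: a true deficit in PSA control is less likely to reach significance. With no HR or confidence interval planned for FFBF, a non-significant p-value would stand alone, and a reader could not tell how large a deficit remains compatible with the data.

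**Working it through.** **1. The plan's own figures.** No power or event count is stated for FFBF or OS. The stated powers concern the primary t-tests (61 per arm, one-sided 0.05). The noncentrality is margin / (SD × √(2/61)): GI 6/(13.2 × 0.1811) = 2.51, GU 5/(10.5 × 0.1811) = 2.63. With 120 df, power is 80.3% (80% stated) and 83.4% (83% stated). 122/0.9 = 135.6, rounded up to 136. All reproduce, and none depends on the log-rank test.

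**2. Endpoint by endpoint.**

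| Endpoint | Test | Regression named |
|---|---|---|
| OS | log-rank, no strata named | Cox |
| TTP (includes biochemical failure) | Gray | Cox; also listed as competing-risk |
| PCSM, LF, RF, DM | Gray | Fine-Gray |
| FFBF | log-rank, no strata named | none |

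**3. Simulation.** From the document: N = 136; 1:1 permuted blocks within EPIC group × ADT × nodal RT, read as 16 cells. Assumed: block size 4; 50% on ADT; 80% agreement between ADT and nodal RT; exponential failure times; 3 to 5 years of follow-up; two-sided 0.05; true arm HR 2 against 5 fractions; 30% biochemical failure at 5 years in the 20-fraction arm without ADT or nodal RT (60% in one scenario).

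At each failure, let a be 1 if the patient who fails is in the 5-fraction arm and 0 otherwise, and let p be the share of those at risk in that arm. Then U = Σ(a − p), V = Σp(1 − p), and the test rejects if |U|/√V > 1.96. The one-step HR is exp(U/V), with U and V summed over runs. The stratified version computes U and V within strata and adds them. Each scenario has 3,000 to 4,000 runs.

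| ADT HR / nodal HR / reference failure | Events | Power: pooled | ADT × nodal | All 16 cells | Gain from ADT × nodal | One-step HR: pooled / ADT × nodal |
|---|---|---|---|---|---|---|
| 1 / 1 / 30% | 46 | 64.2% | 64.2% | 61.1% | 0.0 | 1.99 / 1.99 |
| 0.5 / 0.7 / 30% | 32 | 45.4% | 47.6% | 45.6% | 2.2 | 1.93 / 1.96 |
| 0.3 / 0.6 / 30% | 27 | 37.8% | 41.3% | 39.3% | 3.5 | 1.88 / 1.96 |
| 2 / 1.5 / 30% | 70 | 77.9% | 81.5% | 78.7% | 3.6 | 1.91 / 2.01 |
| 0.3 / 0.6 / 60% | 55 | 61.0% | 70.9% | 66.9% | 9.9 | 1.83 / 1.99 |
| 3 / 2 / 30% | 84 | 69.8% | 86.4% | 82.6% | 16.6 | 1.71 / 2.01 |

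With no arm effect, the pooled test rejects in 5.1% when the factors are not prognostic and in 2.0% to 4.9% when they are. The ADT × nodal test rejects in 4.7% to 5.5%. A rerun with a different random seed gave the same pattern.

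**4. A second set of assumptions.** Here only ADT is prognostic, the test is stratified by ADT alone, 30% to 70% are on ADT, the failure hazard without ADT is 0.12 to 0.20 per year (1 − exp(−0.6) = 45% to 1 − exp(−1) = 63% at 5 years), and follow-up is 5 years. Power, pooled against stratified:

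- ADT HR 0.7: 81.1% and 81.5%
- ADT HR 0.5: 76% and 78%
- ADT HR 0.3: 65% and 71%, or 70% and 78%
- ADT HR 0.5 plus 1.5 years without failures on ADT: 75% and 80%
- ADT HR 0.5 plus 2 such years: 76% and 85%

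**5. Why not all cells.** If ADT and nodal RT form one yes/no factor there are 8 cells, otherwise 16: 136/8 = 17 and 136/16 = 8.5 patients per cell on average. The table shows that stratifying on all 16 gives back part of the gain, and loses about 3 points when nothing is prognostic.

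**The case against.** The strongest reply is that the article never says the test is unstratified, and that a condensed report may leave strata to the full protocol or SAP. That is fair for the single phrase about the log-rank test. It is weaker for the section as a whole, which allots a method to each endpoint, names stratification variables for the adjusted HRs, and puts FFBF in no regression list.

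Several further points stand:

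- The pooled test is valid. Randomising within strata does not make it wrong, and its type I error did not materially exceed 5% in any scenario. A marginal HR nearer to 1 than a conditional one is also a different quantity, not in itself an error.
- A reader might infer that OS is equally exposed. It is not: OS has an adjusted Cox HR, so only its log-rank p-value is involved, and no OS simulation was run.
- A reader might infer that no adjusted evidence on PSA control is planned. TTP counts biochemical failure and is modelled, with baseline PSA and ADT status among the covariates. TTP is a composite, however, adjustment is only as appropriate, and nodal RT is not in the list.
- The strata were chosen for association with the EPIC outcome. Adverse indication and PSA suppression act in opposite directions and could partly cancel, leaving little to gain.

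**Conclusion.** The point holds in a limited form. As written, FFBF is compared by one test that names no strata, with no HR or confidence interval, while the trial randomises by two factors that the article ties to disease risk. If those factors predict PSA failure, pooling attenuates the contrast (one-step HR 1.71 to 1.93 for a true HR of 2, against 1.96 to 2.01 when stratified) and a real loss of control is easier to miss.

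The power loss is about 0 to 4 points for mild to moderate prognostic effects and about 10 to 17 points only for strong effects or high event rates. The ADT-only scenarios with a strong effect or a long suppression period fall between, at 5 to 9 points. All of this rests on assumed prognostic strengths, event rates and a two-sided 0.05 test; the document states none of them for FFBF.

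Two stronger readings are not supported. The test is not invalid. Nor is its conservatism protective: it guards only against falsely declaring a difference, which is not the main worry when the question is whether 5 fractions is no worse. This is a minor matter for one secondary endpoint. It leaves the primary analysis and the sample size untouched.

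**What to change.** In Analysis of secondary endpoints:

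1. State that the FFBF log-rank test, and for consistency the OS one, is stratified by the ADT and pelvic nodal RT factor or factors as declared at randomisation, and not by all randomisation cells.
2. Add FFBF to the endpoints that receive an HR with 95% CI, from a Cox model stratified by or adjusted for the same factors.
3. Add nodal RT to the stratification variables named for adjustment, so that the list agrees with the randomisation section. That section should also say whether ADT and nodal RT are one factor or two.

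Extending stratification to the Gray's tests was not evaluated here and is not part of this recommendation.

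The cost is a few lines of wording and one strata term in the code. No new data are needed, and in the scenario with no prognostic effect, stratifying by ADT and nodal RT lost no power (64.2% either way).

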**Methods:**

A total of 136 patients will be randomized in a 1:1 ratio to salvage MRgRT in 5 fractions or 20 fractions using permuted block randomization. Patients will be stratified according to baseline Expanded Prostate Cancer Index Composite (EPIC) bowel and urinary domain scores as well as nodal treatment and androgen deprivation therapy (ADT). Patients undergoing 5 fractions will receive a total of 32.5 Gy over 2 weeks and patients undergoing 20 fractions will receive a total of 55 Gy over 4 weeks, with or without nodal coverage (25.5 Gy over 2 weeks and 42 Gy over 4 weeks) and ADT as per the investigator’s discretion. The co-primary endpoints are change scores in the bowel and the urinary domains of the EPIC. The change scores will reflect the 2-year score minus the pre-treatment (baseline) score. The secondary endpoints include safety endpoints, including change in GI and GU symptoms at 3, 6, 12 and 60 months from completion of treatment, and efficacy endpoints, including time to progression, prostate cancer specific survival and overall survival.

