#### Primary endpoint

The co-primary endpoints are change scores in the bowel (GI) or urinary (GU) domains of the Expanded Prostate Cancer Index Composite (EPIC). The change scores will reflect the 2-year score minus the pre-treatment (baseline) score.

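### The efficacy-analysis paragraph lists the stratification variables without pelvic nodal radiotherapy, a factor the trial also randomises by (minor)

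*Protocol article*

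**What the plan says.** The stratification factors are described three times in the protocol article.

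- Abstract, Methods: baseline EPIC bowel and urinary scores, "as well as nodal treatment and androgen deprivation therapy (ADT").
- Evaluation of randomization and blinding: four groups formed from high or low EPIC bowel and urinary scores, "as well as pelvic radiotherapy and androgen therapy", the latter given as yes versus no. The reason offered is "for these factors are expected to be associated with the primary outcome".
- Analysis of secondary endpoints, efficacy part: "Baseline PSA, stratification variables (baseline EPIC score and ADT status), age, race, and other covariates (Gleason, T-stage), will be adjusted for as appropriate".

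The last passage governs the adjusted hazard ratios: Cox regression for OS and TTP, and Fine-Gray regression for the competing-risk endpoints. It names baseline PSA, EPIC score, ADT, age, race, Gleason score and T-stage. Nodal radiotherapy is not among them.

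**The concern.** The parenthesis in the efficacy paragraph claims to say what the stratification variables are, and it disagrees with the design. A factor used to balance the arms would normally be carried into the adjusted model. It costs nothing, and fixing it beforehand removes a later choice between adjusted estimates.

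Nodal radiotherapy is also a plausible covariate for these endpoints. Its indications in the Radiation treatment planning section are a PSA above 0.4 ng/ml, a high Decipher score or positive nodes, and neither Decipher score nor nodal stage is a listed covariate. Regional failure is defined by pelvic lymphadenopathy, in the region that nodal radiotherapy treats.

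If a factor matters for the outcome, leaving it out of a proportional-hazards model pulls the hazard ratio for arm toward 1, even when the factor is balanced. Here that would make the two schedules look slightly more alike on progression.

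**Working it through.** **1. The lists side by side.**

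| Factor | Abstract | Randomisation section | Efficacy analysis |
|---|---|---|---|
| Baseline EPIC bowel and urinary | yes | yes (4 groups) | yes, as EPIC score |
| Pelvic nodal radiotherapy | yes | yes | **not named** |
| ADT | yes | yes | yes |

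**2. One factor or two?** The abstract names nodal treatment and ADT separately. The randomisation section puts them together with a single yes/no, which can be read as one joint factor.

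- Two factors: 4 × 2 × 2 = 16 strata, 136/16 = 8.5 patients each.
- One joint factor: 4 × 2 = 8 strata, 136/8 = 17 patients each.

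With two factors, the efficacy list is one short. With one joint factor, calling it ADT status misnames it. Both readings call for a correction.

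**3. The plan's own figures, to see whether they are touched.** Inputs from Sample size and accrual: 61 per arm, one-sided 0.05, margins 6 (GI) and 5 (GU), SDs 13.2 and 10.5. By the normal approximation, power = Φ(margin / (SD × √(2/61)) − 1.645), with √(2/61) = 0.1811.

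- GI: 6/(13.2 × 0.1811) = 2.51; power 0.807 (noncentral t: 0.803). Stated: 80%.
- GU: 5/(10.5 × 0.1811) = 2.63; power 0.838 (noncentral t: 0.834). Stated: 83%.
- 122/0.9 = 135.6, so 136 randomised, as stated.

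All are reproduced, and none uses the efficacy covariate list.

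**4. Size of the effect on an adjusted hazard ratio.** The article gives no efficacy event rates or covariate effects, so every input here is an assumption.

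*Trial-sized simulation* (1,500 trials per setting): 136 patients, permuted blocks of 4 within nodal radiotherapy × ADT strata, baseline hazard 0.055 per year, censoring at 5 years, about 50 to 59 progressions, 50% nodal radiotherapy, ADT HR 0.7, true arm HR 1.8. Nodal-group HR was 2 or 3, and agreement between nodal radiotherapy and ADT was 70% or 90%. The models compared were arm + ADT and arm + ADT + nodal radiotherapy.

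| Setting | Mean HR without | Mean HR with | Gap | Power without | Power with | Gap |
|---|---|---|---|---|---|---|
| a | 1.79 | 1.82 | 0.03 | 51.2% | 53.2% | 2.0 |
| b | 1.83 | 1.85 | 0.02 | 52.4% | 54.0% | 1.6 |
| c | 1.77 | 1.84 | 0.07 | 58.5% | 63.8% | 5.3 |
| d | 1.79 | 1.82 | 0.03 | 58.6% | 61.5% | 2.9 |

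Averaged hazard ratios from small samples are not a clean measure of bias, so only the gaps are informative. The largest gap on the log scale is ln(1.84/1.77) = 0.039. The approximate standard error of a log hazard ratio is √(4/events), which is 0.28 at 50 events and 0.26 at 59. The largest shift is therefore about one-seventh of a standard error.

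*Large-sample check* (10,000 patients, 5 repeats, true arm HR 1.5, balanced factor with prevalence 30% or 50% and its own HR 1.5 to 3.0): about 1.43 to 1.49 without the factor, 1.47 to 1.51 with it. The direction is the same and the shift is again small. Balance rules out confounding; what remains is the attenuation that comes from omitting a covariate in a hazard model.

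**The case against.** Several points can be made for the plan as written.

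- **It may be shorthand.** The General concomitant medication section and the Fig. 1 legend give ADT and nodal irradiation together for the same indications, so ADT status could stand for a joint factor. This remains possible but is not established. The abstract names the two separately and leaves them to discretion, and the inclusion criteria let some patients start ADT during the wait after surgery without mentioning nodal treatment. The two can therefore differ.
- **The rule is permissive.** The covariates "will be adjusted for as appropriate in this analysis", and final model details may sit in an analysis plan that is not shown. That wording governs the variables named; it does not add one that is missing. It does mean that the omission should be described as one in the list, not as a settled feature of the final model.
- **Disease risk is partly covered.** PSA, one of the nodal indications, is adjusted for, as are Gleason score and T-stage. This stands. The trial-sized simulation included none of these covariates, so it probably overstates what nodal radiotherapy would add.
- **More terms can overfit.** Endpoints such as PCSM or local failure may have few events among 136 patients. This also stands and limits the fix.

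A reader might infer that the trial itself calls nodal radiotherapy prognostic for the efficacy endpoints. It does not. The randomisation section ties the factors to the primary outcome, and "The co-primary endpoints are change scores in the bowel (GI) or urinary (GU) domains" of EPIC, which measure toxicity.

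**Conclusion.** The inconsistency is real and minor: the efficacy paragraph's list of stratification variables does not match the design and, as listed, leaves out a factor the trial randomises by.

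Under the assumed inputs, the cost is a shift of 0.02 to 0.07 in the mean hazard ratio and about 2 to 5 points of power, the upper end coming from a single setting. Only progression was simulated, so these figures do not carry over to OS, PCSM, local, regional or distant failure. No standard errors were compared, so no claim about inflated standard errors is made.

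It would be tempting to conclude that the plan would hide an efficacy loss in the 5-fraction arm. The documents do not support this. The trial is powered only for the EPIC endpoints and states no efficacy non-inferiority claim. The Kaplan-Meier and log-rank comparisons and the cumulative-incidence estimates do not use this covariate list. The co-primary t-tests, margins, sample size and power are unaffected.

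**What to change.** 1. State whether nodal radiotherapy and ADT are one stratification factor or two, and use the identical list in the abstract, the randomisation section and the efficacy-analysis paragraph.
2. Include nodal radiotherapy (yes/no), or the joint factor if there is only one, as recorded at randomisation, in the adjusted models for TTP and for other endpoints with enough events.
3. For endpoints with few events, do not force every covariate in. Give the randomisation factors priority over the other covariates, or stratify the model by them. If there are 16 strata averaging 8.5 patients, stratifying on every cell would leave little information, so separate terms for the factors may be preferable.

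The cost is a line of wording and at most one model term. The data are already recorded for randomisation, and no patients, visits or procedures are added.
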